#### Official experiment

This trial is a clinical intervention study, and the primary outcome indicator is the LSAS score. Compare sample size formulae based on means $n=\frac{2^{2}\,{\left(\mu_{\alpha }+\mu_{\beta }\right)}^{2}\,\sigma^{2}}{\delta^{2}}$. Take α = 0.05, β = 0.10. From the pre-test, we can calculate that σ2 = 243.04 and δ2 = 272.25, estimating a sample size of about 62 cases, and considering a 20% missed visit, 62 + 62*0.2 = 74, 74 patients are to be included in the formal trial, 37 in the intervention group and 37 in the control group.

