### Statistical analysis

#### Statistical data collection

The HAMD-17 scale will be administered by a professional psychologist, while the remaining LSAS, SAD, and PSSE scales will be completed on the spot by the assessor who will carefully explain the purpose of the study and the method of completion to the study participants and gain the support and understanding of the patients before completing the questionnaire. The scale assessors will be selected from those who do not perform clinical interventions to reduce bias due to subjective factors. A paper version of the questionnaire is given to inpatients, and patients are followed up by phone or text messages after they are discharged from the hospital. When all the scales have been collected, the information is promptly reviewed and confirmed, and patients are asked to cooperate in correcting any problems found.

Data entry will be carried out by investigators who are not involved in the implementation of the intervention. After the data has been safely collected and entered, the data collected will be statistically analyzed with SPSS 25.0. *P* < 0.05 means the differences are statistically significant.

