The design of the experiment took into account the possibility of changes in the subject’s condition, and thus we set a 20% lost visit to ensure an adequate sample size. The intervention course is arranged in four interlocking sessions to refresh the knowledge taught and apply it to practice, while arranging for the coaches to take the lead and ensure the course is conducted properly, but more so to encourage the hands-on practice by the patients, using the class as an opportunity for patients to communicate and learn from each other, promoting their understanding of each other and helping each other to practice their social skills.

Before the formal trial began, a pre-experiment was conducted to examine both the motivation and cooperation of the study subjects. At the same time, the content of the sessions was improved to make the program more relevant to the actual needs of young people with depression, based on the subjects’ self-specific feelings and evaluations. The pre-experiment followed strictly to inclusion and exclusion criteria for the selection of subjects and was randomized to prevent cross-contamination between subjects. We found that all study participants cooperated positively with the study, were highly compliant and were able to successfully complete all training sessions without dangerous negative emotions or side effects, validating the reliability and safety of the training in this study. After the pre-experiment, social anxiety scores, social avoidance and distress mood decreased in the intervention group compared to the control group, while social self-efficacy scores increased relatively after the intervention, as detailed in Table 3.

**TABLE 3 T3:** The grading of the pre-experiment (n1 = n2 = 6; LASA, Liebowitz social anxiety scale; SAD, social avoidance and distress scale; PSSE, scale of perceived social self-efficacy; HAMD-17, Hamilton depression scale).

Entries	Before the trial		After the trial	
	Intervention group	Control group	Intervention group	Control group
LSAS	55.50 ± 21.20	52.25 ± 20.30	41.75 ± 17.21	51.50 ± 13.90
SAD	22.50 ± 3.64	22.25 ± 3.90	16.25 ± 5.31	22.00 ± 4.30
PSSE	52.2 ± 10.35	43.75 ± 4.66	54.50 ± 7.92	45.00 ± 7.45
HAMD-17	19.25 ± 1.75	19.50 ± 1.19	10.75 ± 1.48	11.50 ± 2.06

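### The stated 62 patients do not follow from the printed formula and inputs under a two-sided test (38 in total), delta is not the pilot's, and 74 enrolled does not cover 20% loss

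*Protocol article*

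**What the plan says.** The sample size text is under Sample size, Official experiment. The article introduces its formula with "Compare sample size formulae based on means" and prints n = 2²(u_α + u_β)²σ²/δ². It sets "Take α = 0.05, β = 0.10". The variance and effect are said to come from the pre-test: "we can calculate that σ2 = 243.04 and δ2 = 272.25". The result is "estimating a sample size of about 62 cases, and considering a 20% missed visit, 62 + 62*0.2 = 74", split as 37 and 37. The text says neither whether α is one-sided or two-sided, nor whether n is a total or a per-arm number.

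Elsewhere, Statistical data collection gives the significance rule only as P "< 0.05 means the differences are statistically significant". Statistical methods plans a repeated measures ANOVA for the LSAS. The Discussion says of the loss allowance that "we set a 20% lost visit to ensure an adequate sample size". Table 3, also in the Discussion, gives the pilot LSAS (six per arm): 55.50 falling to 41.75 (SD 17.21) with the intervention, and 52.25 falling to 51.50 (SD 13.90) in the control group.

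**The concern.** This is the article's only justification of the sample size, and it concerns the primary outcome. A reader who puts the printed inputs into the printed formula, with the two-sided α that an ANOVA F test implies, does not get 62. The effect that drives the calculation is attributed to the pilot but does not match the pilot table. The loss allowance misses its own target.

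At stake is what the trial can detect. If δ = 16.5 is the intended effect, the trial is larger than it needs to be and the shortfall from loss is harmless. If the intended effect is one of those the pilot table shows, power after loss is a little or well below the planned 90%. The text as printed does not let a reader decide between these.

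**Working it through.** **Inputs.** From Official experiment: α = 0.05; β = 0.10 (z = 1.2816); σ² = 243.04 (σ = 15.59); δ² = 272.25 (δ = 16.5); stated N = 62; loss 20%; 37 per arm. From Table 3: the LSAS means and SDs above. Sidedness and the meaning of n are not stated, so both readings of each are run.

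**1. Printed formula, printed inputs.** σ²/δ² = 243.04/272.25 = 0.8927. For two equal arms the per-arm formula has factor 2, so factor 4 gives the total.

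| α | (z_α + z_β)² | 4(z_α + z_β)²σ²/δ² | n read as total | n read as per arm, then doubled |
|---|---|---|---|---|
| Two-sided | (1.960 + 1.2816)² = 10.507 | 37.52 | 38 (19 per arm) | 76 (38 per arm) |
| One-sided | (1.645 + 1.2816)² = 8.564 | 30.58 | 31 (32 for equal arms) | **62** (31 per arm) |

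The plan's 62 is reproduced in one cell only: one-sided α, with the total taken as a per-arm number and doubled. A t-based two-sided calculation gives 19.8, or 20 per arm (40 in total), so the small-sample correction does not explain the gap. 62 exceeds 38 by 24 patients (63%).

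**2. Is δ = 16.5 in the pilot table?**
- Post-trial difference: 51.50 − 41.75 = 9.75.
- Difference in change: (55.50 − 41.75) − (52.25 − 51.50) = 13.75 − 0.75 = 13.0.
- Neither is 16.5. The variance, by contrast, is close to the mean of the two post-trial variances: (17.21² + 13.90²)/2 = 244.7, against 243.04.

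**3. Requirement at each δ** (two-sided, 90% power, σ² = 243.04, n per arm = 2 × 10.507 × 243.04/δ²).

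| δ | δ² | n per arm | Total |
|---|---|---|---|
| 16.5 | 272.25 | 18.76 → 19 | 38 |
| 13.0 | 169.00 | 30.22 → 31 | **62** |
| 9.75 | 95.06 | 53.73 → 54 | 108 |

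So 62 has a second possible origin: a correct two-sided calculation with the pilot difference in change, and δ² misprinted.

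**4. Loss allowance.** 62 × 1.2 = 74.4, taken as 74. After 20% loss, 74 × 0.8 = 59.2, about 3 short of 62. The inflation that retains 62 is 62/(1 − 0.20) = 77.5, or 78 (39 per arm). The loss that 74 can absorb is 1 − 62/74 = 16.2%.

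**5. Power with about 59 analysed** (29.5 per arm, two-sided t test, σ = 15.59). The standard error of the difference is 15.59 × √(2/29.5) = 4.06.

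| δ | δ/SE | Power |
|---|---|---|
| 16.5 | 4.06 | about 98% |
| 13.0 | 3.20 | about 88% |
| 9.75 | 2.40 | about 66% |

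These figures treat patients as independent and compare two means at one time point. Wards, not patients, are randomised here, and the figures make no allowance for that.

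**The case against.** The strongest reply is that 62 can be reproduced and that nothing is lost. The article fixes neither sidedness nor the meaning of n, and one combination gives exactly 62. On the printed inputs, 59 completers exceed the 38 required and give about 98% power, so the sample is ample and the loss slip has no consequence.

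Much of this stands. A reader might infer that 62 cannot be obtained from the printed inputs at all; that goes too far, because the one-sided, doubled route gives it. A reader might also infer that the trial is underpowered, or that the Discussion's claim of an adequate sample is false in substance. The documents do not support that on the printed δ: the shortfall exists only against 62, a number those inputs do not require. Nor is it right that the detectable effect is unknowable. With the printed σ, two-sided α and 90% power, 37 per arm detects about 11.9 LSAS points and about 59 completers detect about 13.4.

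What does not stand is the defence of the passage itself. The route to 62 needs a one-sided α that is declared nowhere and sits badly with a non-directional F test, and it doubles a formula that already gives the total. The reassurance about power depends wholly on δ = 16.5, which the pilot table does not show. That 62 came from δ = 13.0 is equally unproven: it fits, but the article does not say so, and it would combine a difference in change with what looks like a post-trial variance.

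**Conclusion.** Wrong as written. Under the planned non-directional test, the printed formula and inputs require 38 patients in total, not 62. The figure 62 needs either two undeclared steps (one-sided α, and a total treated as per arm) or a δ of 13.0 in place of the printed 16.5. The documents do not settle which, so 38 should not be read as the right sample size for this trial: it is only what the printed inputs yield.

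The loss allowance is wrong on any reading: adding 20% does not cover a 20% loss, and 74 leaves about 59 rather than 62.

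The practical size depends on δ. Power with 59 analysed is about 98% at 16.5, 88% at 13.0 and 66% at 9.75. The loss error alone is small: even at δ = 13.0 it takes power from about 90% to about 88%. The unresolved δ matters far more. All of this assumes σ = 15.59, two-sided α = 0.05, equal arms and independent patients.

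**What to change.** Rewrite the Official experiment paragraph so that formula, inputs and result agree:

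1. State that α = 0.05 is two-sided, and say whether n is per arm or total.
2. Use n per arm = 2(z_0.975 + z_0.90)²σ²/δ².
3. Reconcile δ with Table 3: say whether it is the post-trial difference (9.75), the difference in change (13.0) or something else, and where 16.5 comes from. Use a σ that matches that quantity.
4. Keep 74, but state that about 59 are expected to be analysed after 20% loss, with the two-sided power this gives at the reconciled δ (98%, 88% or 66% for the three values above, under simple individual-level assumptions). Amend the Discussion sentence on the allowance to match.
5. If the sample is inflated instead, divide the reconciled N by 0.80. That gives 78 only if 62 is confirmed as the requirement; from 38 it would be 48.

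The cost is a corrected paragraph and one sentence in the Discussion. No extra patients are needed if 74 is kept and its expected power reported. If 62 completers are confirmed as the requirement and 20% loss is to be covered in full, it is four more patients.

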### Statistical analysis

#### Statistical data collection

The HAMD-17 scale will be administered by a professional psychologist, while the remaining LSAS, SAD, and PSSE scales will be completed on the spot by the assessor who will carefully explain the purpose of the study and the method of completion to the study participants and gain the support and understanding of the patients before completing the questionnaire. The scale assessors will be selected from those who do not perform clinical interventions to reduce bias due to subjective factors. A paper version of the questionnaire is given to inpatients, and patients are followed up by phone or text messages after they are discharged from the hospital. When all the scales have been collected, the information is promptly reviewed and confirmed, and patients are asked to cooperate in correcting any problems found.

Data entry will be carried out by investigators who are not involved in the implementation of the intervention. After the data has been safely collected and entered, the data collected will be statistically analyzed with SPSS 25.0. *P* < 0.05 means the differences are statistically significant.

### Statistical methods

For baseline comparisons, age, LSAS scores, SAD scores, PSSE scores, and total HAMD-17 scores are measurement data for both two groups and will be statistically described using the mean ± S.D., with Paired Sample *T*-Test used to assess between-group balance. The general profile of the test subjects, including gender, education level, occupation, marital status, mode of payment for medical care, per capita household income, type of depression, duration of illness, type of medication, family history, and past history, are all categorical data that will be statistically described using frequencies and percentages, and chi-square tests to assess between-group balance.

The primary outcome indicators (LSAS scores at week 3 and week 6 post-intervention for two groups of patients) and secondary outcome indicators (SAD, PSSE, HAMD-17 scores at week 3 and week 6 post-intervention for two groups of patients) will be compared using Repeated Measures ANOVA to analyze the efficacy of PEERS training at different time periods. Considering the possible interaction between intervention and time, we choose Simple Effects to analyze the different effects of different time variances on PEERS training.

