### Assignment of intervention

Prior to the start of the intervention, different ward were randomly divided into intervention and control groups using a coin toss by an investigator not involved in the implementation of the intervention to prevent contamination, and eligible subjects were sought within the respective ward.

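### A paired-sample t-test is named for the between-arm baseline comparison of five continuous variables, although the arms contain different, unmatched patients

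*Protocol article*

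**What the plan says.** The Statistical methods section lists the continuous baseline variables: "For baseline comparisons, age, LSAS scores, SAD scores, PSSE scores, and total HAMD-17 scores are measurement data for both two groups". It summarises them by mean and SD and compares the arms "with Paired Sample *T*-Test used to assess between-group balance". For eleven categorical characteristics, from gender and education to family and past history, the same paragraph uses "chi-square tests to assess between-group balance".

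The section Assignment of intervention describes how the arms arise: "different ward were randomly divided into intervention and control groups using a coin toss", after which "eligible subjects were sought within the respective ward". The Official experiment section plans "37 in the intervention group and 37 in the control group". The significance threshold given under Statistical data collection is 0.05.

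**The concern.** A paired t-test analyses within-pair differences, so each observation in one arm needs a specific partner in the other. Nothing in this design supplies partners. Software would pair the values in whatever order they sit in the file, and two analysts holding the same data in different row orders would report different P values.

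What is at stake is the credibility of the baseline table for age and the four scales, including the primary scale. Because whole wards are allocated, readers will look closely at that table. A wrong test there could produce or hide a nominally significant imbalance for no reason connected with the patients.

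**Working it through.** **1. Is there any pairing in the design?** Setting the sections side by side:

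- Assignment of intervention: wards are allocated by coin toss and patients are then found within their ward. No matching of patients is mentioned there or elsewhere.
- Statistical methods, continuous variables: a paired test.
- Statistical methods, categorical variables: chi-square tests, which treat the same two arms as independent.

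The sentence on the paired test concerns baseline only and gives its purpose as balance between groups, so it cannot be read as a before-after test within an arm.

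**2. Degrees of freedom at the planned size.**

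- Paired: 37 − 1 = 36, two-sided 5% critical t = 2.03.
- Independent samples: 37 + 37 − 2 = 72, critical t = 1.99.

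The loss of degrees of freedom alone therefore costs little.

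**3. Where the arbitrariness enters.** With n per arm, both tests have the same numerator, the difference in means. They differ in the variance:

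- independent: (s₁² + s₂²)/n
- paired: (s₁² + s₂² − 2·r·s₁·s₂)/n

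Here r is the correlation between values that happen to share a row. When the SDs are similar, t(paired) ≈ t(independent)/√(1 − r). Under random row order r has mean 0 and SD 1/√(n − 1) = 1/√36 ≈ 0.17, so about 95% of orderings give r between −0.33 and +0.33.

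**4. Size in one example.** The plan states no figure for the balance check, so there is none to reproduce. One data set was simulated with 37 per arm from normal distributions with the pilot baseline LSAS values in Table 3 (55.50 ± 21.20 and 52.25 ± 20.30).

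- Independent-samples test: t = 1.78 on 72 df, P = 0.079.
- Paired test on the same data, 10,000 random re-pairings: median P 0.084, central 95% 0.038 to 0.129, extremes 0.005 and 0.173.
- Share of re-pairings with P below 0.05: about 8%.

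The formula in step 3 agrees. With r = +0.33, t ≈ 1.78/√0.67 ≈ 2.17, P ≈ 0.037 on 36 df. With r = −0.33, t ≈ 1.78/√1.33 ≈ 1.54, P ≈ 0.13.

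**5. Error rate over many trials.** In 100,000 simulated data sets with no true difference and random pairing, the paired test rejected in 5.0% and the independent-samples test in 5.0%. If the rows of each arm were sorted by the variable being tested, the paired test rejected in about 69%. The plan does not say that rows would be sorted, so this shows only how far the result can depend on file order.

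**The case against.** The best defence is that this is a slip in naming. The purpose is clear, the parallel chi-square tests are unpaired, and an analyst would probably choose the right menu item. The sentence governs baseline description only. This limits the weight of the point, but a specific test is named and it is the wrong one, so the text still needs correcting.

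Four stronger readings are tempting, and the documents do not support them:

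- **That the false-positive rate is inflated.** With random pairing it stays near 5%. The defect is an undefined pairing and a P value that is not unique to the data.
- **That this is the plan's only protection against baseline differences.** Eleven other characteristics are checked by chi-square tests, which are unaffected. The scales are also measured at baseline, and an interaction of intervention with time is considered. Whether baseline enters that model is unclear, because Statistical methods names only the week 3 and week 6 scores.
- **That patients will be discarded.** This happens only if the arms are unequal. Equal arms of 37 are planned, and later loss to follow-up does not remove baseline values.
- **That conclusions will commonly flip.** In the example the independent-samples P was already close to 0.05, and about 92% of re-pairings stayed above the threshold. A P value far from 0.05 would seldom cross it.

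**Conclusion.** The error is real and its reach is narrow. The paired t-test cannot be meaningfully applied to these two arms, and the resulting P values for age, LSAS, SAD, PSSE and HAMD-17 at baseline would depend on row order. The numerical illustration rests on one simulated data set with normal values, pilot means and SDs, and 37 per arm; other data would give other ranges. The sample size, the significance level and the repeated measures ANOVA of the outcomes do not depend on this sentence. It should be corrected before the baseline table is produced, but it gives no reason to doubt the primary analysis.

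**What to change.** In Statistical methods, replace the paired-sample t-test by an independent-samples t-test, in the Welch form if the variances differ. Alternatively, drop the test and report means, SDs and standardised differences by arm. Either change is one line of text, needs no new data, and leaves the sample size and significance level as they are.

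As a separate improvement that does not follow from the wrong test name, the outcome model can be adjusted for the baseline score, which is already collected. An independent-samples test would still ignore the allocation by ward; that is a different point and this correction does not address it.

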**Materials and methods and analysis:**

The aim of this trial protocol is to evaluate the efficacy of the localized PEERS training program on social competence, depressed mood in a Chinese young adult population with depression. The primary outcome will be a change in self-reported depressive symptoms from baseline to week 3 post-randomization to week 6 post-randomization measured using the Liebowitz social anxiety scale (LSAS). Secondary outcomes include the rate of decline in severe social anxiety, the Social Avoidance and Distress Scale (SAD), the Social Self-Efficacy Scale (PSSE), and the Hamilton Depression Scale (HAMD-17). Data for each assessment will be collected at baseline, week 3 of the trial, and week 6 of the trial.

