### Outcome measure

The measurement of each scale measure, the outcome indicators will all be carried out by investigators who are not involved in the implementation of the intervention.

A baseline survey will be conducted by the investigator after the study subjects are identified, and basic information will be collected on the subjects, including age, gender, marital status, mode of payment (self-pay, agricultural insurance, medical insurance, and others), type of depression (general depressive disorder, anxiety depressive disorder, and others), previous history, family history, duration of illness and medication use, etc.

Considering that the first onset of action of antidepressants is between 2 and 4°weeks (46), We, therefore, chose to collect the subjects’ depression scores at three-time points: baseline, week 3 of the intervention and week 6 of the intervention. The scales were selected based on clinical applicability and reliability to dynamically assess the efficacy of the localized PEERS training.

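### The efficacy analysis gives the baseline score no stated role beyond a balance test, so no reading of it yields a baseline-adjusted difference at week 3 or week 6

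*Protocol article*

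**What the plan says.** The Statistical methods section defines the primary outcome as "LSAS scores at week 3 and week 6 post-intervention for two groups of patients" and treats SAD, PSSE and HAMD-17 in the same way. These outcomes "will be compared using Repeated Measures ANOVA to analyze the efficacy of PEERS training at different time periods". For a possible interaction of intervention and time, the authors add that "we choose Simple Effects to analyze the different effects of different time variances on PEERS training". No covariate, change score or baseline term is named. In that section, baseline scores appear only in a test "used to assess between-group balance".

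Elsewhere, baseline is given more weight. The Outcome measure section has scores collected at "baseline, week 3 of the intervention and week 6 of the intervention". The Secondary outcome section administers SAD, PSSE and HAMD-17 at the same three times in order to compare changes. The Abstract words the primary outcome as a change "from baseline to week 3 post-randomization to week 6 post-randomization measured using the Liebowitz social anxiety scale (LSAS".

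Under Assignment of intervention, "different ward were randomly divided into intervention and control groups using a coin toss", and eligible patients were then sought within each ward. The number of wards is not given.

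**The concern.** The baseline score is usually the strongest available predictor of the follow-up score. Leaving it out of the efficacy model has two costs.

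- **Imbalance.** Any baseline difference between the arms passes in part into an unadjusted comparison at follow-up. In this trial such a difference could arise by chance, because wards are allocated rather than patients. It could also arise by selection, because patients are identified once the ward's arm is known. A balance test may detect a difference but does not remove it from the estimate.
- **Precision.** The estimate is more variable than the collected data require.

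The article commits itself to a method and to the scores it is applied to, so this is more than a detail left for a later plan.

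**Working it through.** **1. What each reading of the plan estimates**

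| Reading | Between-group result | Baseline-adjusted? |
|---|---|---|
| Weeks 3 and 6 only | Group effect, and simple effects at each visit, on raw scores | No |
| Baseline as a third level, simple effects of group | Raw score difference at each visit | No |
| Baseline as a third level, group x time | Difference in change; the mean baseline gap is removed | Not as a covariate |

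Simple effects of time within each arm give no between-group difference at all.

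**2. Inputs**

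- Official experiment: σ² = 243.04, so SD = √243.04 = 15.59; δ² = 272.25, so δ = 16.5; 62 patients before allowance for loss, so 31 per arm; "Take α = 0.05, β = 0.10".
- Table 3, pilot LSAS: before, 55.50 (SD 21.20) against 52.25 (SD 20.30); after, 41.75 against 51.50. The difference after treatment is 51.50 − 41.75 = 9.75.
- Assumptions, not in the document: baseline/follow-up correlation r = 0.3 to 0.7; equal SD of 15.59 at each visit; two-sided α (the article does not state sidedness); no ward clustering.

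**3. The plan's own figure**

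The printed formula is 4(z_α + z_β)²σ²/δ². With one-sided α it gives 4 × 8.564 × 243.04/272.25 = 30.6, or 31. The stated 62 follows only if this 31 is read as per arm and doubled. With two-sided α the formula gives 37.5. The 31 per arm is used below only as the plan's stated size; the point does not depend on how it was derived.

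**4. Variance at one visit, relative to the raw-score comparison**

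Covariate adjustment: 1 − r². Change from baseline: 2(1 − r).

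| r | Adjusted | Change |
|---|---|---|
| 0.3 | 0.91 | 1.40 |
| 0.5 | 0.75 | 1.00 |
| 0.7 | 0.51 | 0.60 |

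Adjustment beats both alternatives throughout this range. The ratio of change to adjusted variance is 2/(1 + r), which exceeds 1 whenever r is below 1.

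**5. Power at week 6 (31 per arm, two-sided 0.05, noncentral t)**

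The unadjusted standard error is 15.59 × √(2/31) = 3.96. The other standard errors are this value times the square root of the ratio in step 4.

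| Difference | Raw score | Adjusted, r = 0.3 / 0.5 / 0.7 | Change, r = 0.3 / 0.5 / 0.7 |
|---|---|---|---|
| 9.75 (pilot) | 68% | 72 / 80 / 92% | 53 / 68 / 88% |
| 16.5 (planned) | 98% | 99% / over 99% / over 99% | 93% / 98% / over 99% |

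**6. What a baseline gap does to the estimate**

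A gap of g points is expected to shift a raw follow-up difference by r × g. For a gap the size of the pilot's (55.50 − 52.25 = 3.25), that is 1.0, 1.6 and 2.3 points at r = 0.3, 0.5 and 0.7.

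**The case against.** Repeated-measures ANOVA is a recognised method, and covariates are often settled in a later document. That is fair as far as it goes. But this article names the scores, the test and the follow-up comparisons, and none of them is baseline-adjusted.

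Four stronger readings are tempting, and the document does not support them.

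- **That baseline is definitely left out of the ANOVA.** The Abstract and the Outcome measure and Secondary outcome sections allow it as a third level. The group x time test would then remove the mean baseline gap, so imbalance would not reach that test. What remains is the lower efficiency shown in step 4, and the unadjusted simple effects.
- **That the main test is diluted by a visit at which no effect can exist.** This would apply to a group main effect over three visits. The article does not name that effect as its test; it points to the interaction and to simple effects.
- **That the trial is seriously underpowered for this reason.** At the planned 16.5 points the unadjusted comparison already has about 98% power before clustering. The gain matters if the true effect is nearer the pilot's 9.75.
- **That the pilot shows imbalance between wards.** With six per arm, the standard error of the baseline difference is √((21.20² + 20.30²)/6) = 12.0, so 3.25 points is 0.27 standard errors, which is ordinary noise. The Discussion says the pilot was randomized, but not by ward. The move from 9.75 on scores to 13.0 on change is the change-score shift; covariate adjustment would be expected to move the estimate by the 1.0 to 2.3 points in step 6.

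**Conclusion.** The point holds in a limited form. The Statistical methods section gives baseline no role beyond a balance check, the rest of the article leaves that role unclear, and no reading produces a baseline-adjusted difference at week 3 or week 6. Recruitment after ward allocation makes baseline differences plausible, though nothing in the document shows that they will occur.

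The variance saving is 9% to 49% at one visit for r between 0.3 and 0.7. In power it is worth 4 to 24 percentage points at a 9.75-point effect, and about 1 to 2 points at the planned 16.5. The correlation is assumed, and the figures take a common SD of 15.59 and no clustering.

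A reader might infer that adjustment would deal with ward differences in general. It would not: it removes the part carried by the patient's own baseline score and leaves clustering and other ward effects untouched. The change is worth making because it is nearly free, not because the planned analysis is invalid for want of it.

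**What to change.** In Statistical methods, state the role of baseline and adjust for it. Suggested wording: *Each outcome (LSAS, SAD, PSSE, HAMD-17) at weeks 3 and 6 will be analysed in a repeated-measures model with group, visit and group x visit, and with the baseline score of the same outcome as a covariate. Baseline will not be a level of the outcome. Adjusted between-group differences at week 3 and week 6 will be reported with 95% confidence intervals.* Bring the Abstract's description of the primary outcome into line with this.

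The cost is a change of wording before the data are analysed. The baseline scores are already collected, and the choice of primary visit need not change. How the model should allow for wards has to be settled separately.
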